### Ethical Considerations

The current SW-CRT is approved by the institutional review board of Louisiana State University (IRBAM-21-1391) and funded by the Gulf Research Program of the National Academies of Sciences, Engineering and Medicine. All enrollees will provide informed consent. The trial has been registered on ClinicalTrials.gov (NCT06093737) and is following the SW-CRT extension for the CONSORT-SPI (Consolidated Standards of Reporting Trials–Social and Psychological Intervention) guidelines for reporting (see Figure 2 for the flow diagram) [77-79].

Research staff and coinvestigators will undergo human subjects training by completing the Collaborative Institute Training Initiative social and behavioral health training module. Individual data are confidential; however, as a community group-based intervention, cluster- and individual-level participation itself is not. To account for differential exposure times between clusters inherent to a SW-CRT design, we will clearly communicate timelines to manage expectations and provide adequate referrals to mental health resources.

To ensure data confidentiality, participants’ responses will be self-reported, and a unique identifier will be assigned to link surveys from the same participant across time. With regard to the qualitative data, at the start of each session of the COPE intervention, participants will discuss confidentiality guidelines, emphasizing respect for privacy to minimize risks of unintentional disclosures. Similarly, at the start of each focus group and interview, confidentiality will be discussed as part of the informed consent process. After transcription of qualitative data, names will be replaced with pseudonyms.

Only the researchers listed on the institutional review board approval will explain, collect, and manage informed consent. Before initial data collection, researchers will explain the study’s purpose, procedures, potential risks, benefits, and right to refuse, as well as the limits of confidentiality, using a plain language script developed by the authors with feedback from the strategy team. In addition, we will allow time for question and answer to ensure participants understand the information before consenting. Researchers will collect signed consent forms that are stored in a locked filing cabinet separate from the data. A reminder of their rights as research participants will be provided before each subsequent assessment, even though signatures are only collected at the initial assessment. Enrollees of both trial arms will be compensated for participation with a US $10 gift card provided for each survey, to a potential total of US $50, and food provided at each in-person or data collection session. CFs will also sign their informed consent to participate in their initial training, be compensated for their time in training and facilitation at a rate of US $600 per series plus US $400 for training (1-time payment, approximately US $50 per hour), and be provided all materials required for facilitation.

**Figure 2 figure2:**
[figure not shown]
Communities Organizing for Power through Empathy (COPE) stepped-wedge cluster randomized trial enrollment flow diagram.

### Sampling Strategies and Sample Size

Multilevel mixed methods, with convenience, purposive, and probability sampling techniques at different levels of analysis, in this case clusters and individuals, will be used as different strategies are required for each aim. Convenience sampling will be applied in the initial phases of the study during the adaptation process to pilot-test the COPE intervention’s components with accessible participants from across the clusters to ensure broad acceptability and commitment to participation in the SW-CRT. For aim 1, maximum variation sampling will be used to gain perspectives from a heterogenous pool of participants and facilitators [80]. This will include purposive sampling of participants from different institutions to gain a diverse set of perspectives on barriers or facilitators that impact implementation of COPE.

For the SW-CRT component of aim 2, we did a power analysis to estimate the required sample size for a target power of 80%. We assumed a standardized moderate effect size of 0.3, 5 time points, a conservative intraclass correlation coefficient (ICC) of 10% (10% site-level and 90% person-level variation), and a within-person correlation of 0.3. The power analysis results indicated that 300 participants at 15 sites with 20 participants per site achieves the target power. We also did sensitivity analyses varying the effect size, ICC, within-person correlation, and number of sites, and with very conservative estimates the target power can be achieved.

After clusters are randomized into groups, participants will be recruited by CFs and project staff using convenience sampling techniques. As one cluster includes a large Spanish-speaking population among its membership, COPE will be delivered to participants in that cluster in Spanish by native Spanish-speaking bilingual facilitators and participants will be provided materials in Spanish.

### Study Setting, Participants, and Eligibility Setting

Louisiana, overall, is estimated to be affected with higher rates of mental health conditions than the national population. As of February 2021, about 715,000 adults in Louisiana had a mental health condition [81]. Nearly half (47.5%) had reported symptoms of anxiety or depression and, that same year, 720 lives were lost to suicide [81]. Despite this need, approximately 3.4 million people in Louisiana lived in a community without sufficient mental health providers [81]. In 2022, about 16% of adults in East Baton Rouge Parish reported experiencing frequent mental health distress [82].

The trial is being conducted at TBR and the cluster CBO locations. The inclusion and exclusion criteria for trial participants are listed in Textbox 1.

Eligibility criteria.
**Inclusion criteria**
Currently aged ≥18 yearsStaff, members, or affiliates of a community-based organization (CBO) affiliated with Together Baton Rouge (TBR)Willing to participate in the intervention
**Exclusion criteria**
Not aged ≥18 yearsNot staff, members, or affiliates of a CBO affiliated with TBRUnwilling to participate in the intervention

### Recruitment and Enrollment

CBO clusters are members of TBR selected to account for geographic and socioeconomic diversity. Clusters are enrolled by program staff who work with the CBO leadership to identify qualified CFs and enroll eligible participants. Engagement efforts emphasize building relationships with trusted local leaders and inclusive outreach that uses culturally relevant materials and ensures transparency. CFs deliver the intervention and recruit participants. Licensed mental health professionals (eg, licensed master or clinical social worker, licensed professional counselor, or licensed marriage and family therapist) or individuals with experience in group or community facilitation, who are affiliated with a TBR institution, and who are willing to commit to the training and delivery of all components of the intervention are eligible to be a CF. To every extent possible, CFs are members or strongly affiliated with the cluster where they are delivering the COPE intervention. In some cases, however, trained CFs may facilitate for a cluster with which they are not strongly affiliated.

Potentially eligible participants will be recruited by the CFs and leaders at each participating cluster CBO. This will be accomplished by a combination of posting fliers, announcements at critical meetings, word of mouth, phone, and social media, as appropriate to each cluster. Enrolled participants will be those who signed the informed consent and completed the baseline (T1) assessment.

### Intervention Arm: COPE

COPE is a 3-session group psychoeducational workshop series we developed that combines psychoeducation and peer support strategies to effect individual, interpersonal, community, and ultimately, societal change. The primary COPE session (C1) is adapted from the RCHC [63] curriculum developed by the second author (TP) and colleagues to provide psychosocial support to professional caregivers, specifically health care and social service providers. During the COPE adaptation, we engaged a team of mental health professionals from diverse backgrounds (in terms of race and ethnicity, gender, national origin, age, and primary language) in a collaborative process to tailor the RCHC to fit the unique needs of Gulf Coast communities at risk of or having survived disasters. Key elements of the adaptation include illustrated materials to engage varied literacy levels and language backgrounds, addition of content on historical and systemic trauma, and incorporation of activities on how to support individuals in distress and build community support.

As illustrated in the COPE conceptual model in Figure 3, the 3 sessions are designed to increase well-being at the individual (coping capacity), interpersonal (social support), and community (engagement) level and decrease adverse individual-level mental health outcomes (perceived stress, anxiety, and depression). Designed to normalize common reactions to stress after traumatic events, the psychoeducational component includes information on stress reactions and their biophysical components (eg, neurological trauma response), reactions common to caregivers, and adaptive coping strategies. The curriculum is grounded in active learning principles, engaging participants in Socratic dialogues about concepts and practical activities. In addition, COPE delivery integrates a group practice model that allows for within-group dialogue, social learning, and cooperation to support group reinforcement of positive change [83]. Through group process incorporated with the discussion of psychoeducational components, COPE helps to reduce isolation by creating an environment in which participants share their experiences and support each other, thus strengthening relationships and social networks.

As shown in Figure 4, the COPE series consists of the primary session 1 (C1, 4 h), focused on recognizing stress in oneself and developing healthy coping strategies while simultaneously building relationships to increase social and community support, and 2 additional follow-up sessions (C2 and C3, 90 min each). Each workshop session engages participants in group exercises that provide information in stress and trauma, skills training on recognizing and supporting individuals exhibiting distress, identifying and developing healthy coping strategies, and identifying and building community-based support.

The second session (C2) focuses on supporting individuals in distress and the third (C3) focuses on building community support. More specifically, session 2 (C2) centers skill building for nonspecialists to increase their capacity to provide basic psychological support to individuals in distress, and it incorporates an interactive role play to provide an opportunity to practice skills learned. Session 3 (C3) centers community resilience, engaging participants in an interactive discussion to name community assets and then map those available within the geographic area of their institution. COPE has been standardized in a single manualized curriculum with accompanying large-format illustrated posters laminated for interactive use and participant workbook [10]. The COPE participant workbook has been translated into Spanish and validated using back translation. For the SW-CRT, assessments will be conducted before each session.

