**Methods:**

The Consolidated Framework for Implementation Research guides our analysis of data collected from surveys, fidelity and field notes, interviews, and focus groups to examine aim 1. We examine aim 2 primarily via a 2-arm pragmatic stepped-wedge cluster randomized trial (SW-CRT) with individuals (approximately n=300) in clusters (faith-based and secular community-based organizations; approximately n=15) in a disaster-prone community in the US Gulf Coast. The cluster-based design implemented in steps supports the community-based nature of the study where timelines differ by organization. A total of 5 self-assessments will be conducted both in person and via email at later time points. We will integrate mixed methods in our analyses for aim 1 by combining themes from interviews and focus groups with implementation measures, and for aim 2 by constructing a data matrix to combine findings from the SW-CRT with thematic analyses of field notes and interviews.

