To accomplish aim 1, we are using the Consolidated Framework for Implementation Research [76] to examine factors that affect intervention implementation and program efficacy, as well as standardized measures of perceptions of feasibility, acceptability, and cultural appropriateness. We will conduct quantitative assessments, interviews, and focus groups with community facilitators (CFs), institutional leaders, and participants (see Multimedia Appendix 1 for facilitator interview guide). In addition, to align with our CBPR approach, our research team includes a group of community members we refer to as the “CBPR strategy team” who guided the adaptation process that developed COPE and will guide the study design, implementation, and analysis of findings. For example, we presented them with options for measures of mental health and discussed the overall survey design. The team chose measures and approved the final survey instrument. We also worked with the team to discuss options for implementation of the COPE sessions and recruitment. As we analyze data, we will review findings and papers developed with the team, along with other community members. In our analyses for aim 1, we will integrate the methods by combining themes from interviews and focus groups with analyses of implementation measures.

To accomplish aim 2, we are collecting cohort data from participants in clusters in both arms assessed along measures of mental health, coping, social support, and community resilience at 5 time points (see Figure 1 for study design and data collection time points). Participants will complete assessments at each time point before content delivery using Qualtrics survey software loaded on a tablet. In cases where participants are unable to use a tablet (eg, discomfort with technology or visual impairment), they will complete the assessment on paper and research staff will enter the data into the software. Participants will be given a US $10 gift card at the completion of each questionnaire.

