### Attention Control Arm: House Meetings

Parallel to the intervention arm, participants in clusters randomized to the control arm will complete assessments before content delivery at the first 3 time points. After the first 2 assessments, they will participate in house meetings—group deliberative conversations, sometimes referred to as listening sessions—following a model regularly practiced by TBR [84,85] before participating in the COPE intervention at their third meeting and just after completing their third assessment. The house meeting is a group session that lasts approximately 1.5 hours and engages participants in a discussion about a specific question posed by the facilitators. At the first house meeting, and after administering the first assessment, participants are prompted to discuss “How are you a caregiver in your everyday life? What does it mean to you to be a caregiver?” or a similar question. Each participant is encouraged to share at least once. The facilitator is not necessarily a mental health professional, and no therapy is provided. At the end of the house meeting, participants are reminded of the date for the next meeting. The second house meeting follows the same protocol with a modified prompt question. After completing the third assessment, participants engage in the COPE intervention.

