**Process evaluation**				
	Acceptability of Intervention	—	Acceptability	Weiner et al [86], 2017
	Intervention Appropriateness	—	Appropriateness	Weiner et al [86], 2017
	Feasibility of Intervention	—	Feasibility	Weiner et al [86], 2017

^a^Not applicable.

To address aim 2, we will collect cohort data on the outcome measures at the 5 assessment time points of the SW-CRT: baseline (T1), before session 2 (T2; 1 m after baseline), before session 3 (T3; 2 m after baseline), after the series (T4; 1 month after session 3), and 6 months after the series (T5). Figure 1 provides a visual of the design and timeline of survey measures. As the control arm switches to the COPE intervention after the T3 assessment, assessments pause until 1 month after session 3 so that T4 assessments align (Figure 1). Both arms complete the T5 assessment 6 months after session 3. As part of the CBPR process, the CBPR strategy team deliberated on the outcomes and measurements, coming to consensus on the final survey.

The primary outcomes and their measures assess individual mental health. Perceived stress is assessed with the Perceived Stress Scale (PSS), a 10-item scale that measures the degree to which a person rates situations as stressful [88], for example, how often respondents find their lives “unpredictable,” “uncontrollable,” or feel “overloaded.” Responses are scored on a 5-point Likert scale ranging from 0 (never) to 4 (very often). Total PSS scores range from 0 to 40, with higher scores reflecting higher perceived stress [91]. The 10-item Perceived Stress Scale has high internal reliability (Cronbach α=0.78-0.90) and has been translated and tested in >25 languages [88,91]. Depression, anxiety, and stress are measured with the Depression, Anxiety, and Stress Scale (DASS-21), a set of 3 self-report scales [87]. The 21 DASS-21 items ask about the presence of symptoms over the past week on a scale from 0 (did not apply to me at all) to 3 (applied to me very much or most of the time) [92,93]. Depression scores range from 0 to 4 (normal), 5 to 6 (mild), 7 to 10 (moderate), 11 to 13 (severe), and >14 (extremely severe). Anxiety scores range from 0 to 3 (normal), 4 to 5 (mild), 6 to 7 (moderate), 8 to 9 (severe), and >10 (extremely severe). Stress scores range from 0 to 14 (normal), 15 to 18 (mild), 19 to 25 (moderate), 26 to 33 (severe) and >34 (extremely severe). The DASS-21 has shown high internal reliability (Cronbach α=0.72-0.91) [92-94].

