#### Aim 2: Testing of Intervention Effects

Aim 2 will test the effectiveness of the COPE intervention on improvements in mental health symptoms (perceived stress, depression, anxiety, and stress), coping self-efficacy, perceived social support, and community resilience (see Table 1 for measures). The SW-CRT design involves clusters sequentially transitioning from control to intervention, allowing for within-cluster comparisons and accounting for time-dependent effects. The primary analysis for aim 2 will follow an intent-to-treat approach using a linear mixed model to examine within- and between-group differences across time. Missing data will be handled under the assumption that they are missing at random, using restricted maximum likelihood estimation, and we will assess the benefit of multiple imputation across missing values and conduct sensitivity analyses. The linear mixed model will account for the hierarchical structure of the data (eg, individuals, clusters, and time), and include fixed effects for the intervention arm, time, and covariates, such as age, ethnicity, and education. We will also include a random intercept for the clusters to assess between cluster variability and random slopes for time given the variability in time points between the clusters.

At time points 4 and 5, participants in the control arm will have transitioned to the intervention arm. To account for this transition, participants will be categorized based on their current condition (control or intervention) at each time point. This approach ensures that the analysis reflects the condition under which participants were exposed during each survey period. We will also conduct a sensitivity analysis to compare outcomes across time points 1 to 3 (before the switch) to time points 4 to 5 (after the switch). This will allow us to examine intervention effects during the period that the control group is unexposed to the COPE intervention. Results will be presented as regression coefficients with 95% CIs and *P* values, ICCs, and variance estimates for random effects.

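### T2 and T3, the only post-baseline assessments with an unexposed comparator, are collected at the arms' own sessions, so missing scores may differ by arm and depend on the outcome

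*Protocol article*

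**What the plan says.** The protocol article ties the early assessments to the meetings in four places.

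- Intervention Arm: COPE: "For the SW-CRT, assessments will be conducted before each session".
- Overview and Study Design: "Participants will complete assessments at each time point before content delivery using Qualtrics survey software loaded on a tablet", with paper as the fallback for people who cannot use a tablet.
- Attention Control Arm: House Meetings: "participants in clusters randomized to the control arm will complete assessments before content delivery at the first 3 time points".
- Study Outcome Measures (text after Table 1) defines the visits by session: "before session 2 (T2; 1 m after baseline), before session 3 (T3; 2 m after baseline".

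The one remote route is in the Abstract, Methods: "A total of 5 self-assessments will be conducted both in person and via email at later time points". Which time points count as later is not said.

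Overview and Study Design has control clusters switch to COPE after the third assessment. Aim 2: Testing of Intervention Effects adds: "At time points 4 and 5, participants in the control arm will have transitioned to the intervention arm". On analysis, that section says "The primary analysis for aim 2 will follow an intent-to-treat approach", using a linear mixed model fitted by restricted maximum likelihood (REML) with data assumed missing at random. The benefit of multiple imputation will be assessed and sensitivity analyses run. Neither clusters nor participants are blinded.

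**The concern.** Only at T2 and T3 can people exposed to COPE be set against people not yet exposed, and under the stated rule a score at those visits requires being in the room. Attendance is decided after randomisation by people who know their arm. By T2 they have sat through either a 4-hour COPE session or a house meeting of about 1.5 hours. At T3 the control arm is about to start COPE, while the COPE arm is at its last session. The reasons to come or stay away may therefore differ by arm.

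If the choice also depends on how distressed a person is at that visit, the missing score is related to its own value beyond what the observed data explain. The missing-at-random likelihood does not correct for that. More distress-related skipping in the COPE arm would overstate the benefit; more in the control arm would understate it.

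**Working it through.** **1. The plan's own figure.** Sampling Strategies and Sample Size gives 15 sites of 20, effect 0.3 SD, 5 time points, ICC 0.10, within-person correlation 0.3 and target power 80%. Alpha and model are not stated. I assume two-sided 0.05, 8 sites starting with COPE and 7 with house meetings, time as categories, exposure coded by current condition, and variances of 0.10 (cluster), 0.20 (person) and 0.70 (residual), reading 0.3 as the total within-person correlation. The standard error with complete data is 0.0867, so power = Φ(0.3/0.0867 − 1.96) = Φ(1.50) = 0.93. That agrees with the statement that the target is achieved, but allows for no missed visits.

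**2. How much rests on T2 and T3.** Exposure over T1 to T5 is 0,1,1,1,1 in the COPE arm and 0,0,0,1,1 in the control arm. Without T2 and T3 both arms read 0,1,1. That equals the sum of the T4 and T5 time indicators, so the effect is not estimable (design rank 3 of 4). T1 to T3 alone give a standard error of 0.1086. Their share of the information is (0.0867/0.1086)² = 0.64, and power on them alone is Φ(0.3/0.1086 − 1.96) = 0.79.

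**3. Size of the bias, under assumptions.** The documents give no attendance rate. Suppose a share s skips a visit, and skipping has correlation g with the visit-specific residual of the distress score. The mean residual among those observed is then lower by

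g × √0.70 × φ(z)/(1 − s), where z cuts off the upper share s of a standard normal.

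- s = 0.30: φ(z) = 0.348; 0.348/0.70 = 0.497; × 0.837 = 0.416 g.
- s = 0.15: φ(z) = 0.233; 0.233/0.85 = 0.274; × 0.837 = 0.229 g.
- Excess in the COPE arm: (0.416 − 0.229) g ≈ 0.186 g, which is 0.056 SD for g = 0.3 and 0.093 SD for g = 0.5.

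A shift common to T2 and T3 passes in full into the estimated effect. A simulation analysed with the planned kind of likelihood (200 runs per scenario, simulation error about 0.007 SD) agrees:

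| Skipping, COPE / control | g, COPE / control | Estimate when true effect is −0.30 | Estimate when true effect is 0 |
|---|---|---|---|
| 30% / 15% | 0 / 0 | −0.314 | 0.003 |
| 40% / 20% | 0 / 0 | −0.301 | −0.001 |
| 20% / 20% | 0.3 / 0.3 | −0.308 | 0.005 |
| 30% / 15% | 0.3 / 0.3 | −0.351 | −0.061 |
| 30% / 15% | 0.5 / 0.5 | −0.391 | −0.091 |
| 30% / 15% | 0.3 / 0 | −0.424 | −0.123 |
| 20% / 20% | 0.5 / 0 | −0.450 | −0.142 |

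In the fourth and fifth rows the simulated type I error was 12.5% and 13.5% (simulation error about 2.4 points). A normal approximation with standard error 0.0955 gives about 9% for a bias of 0.056 and 16% for 0.093.

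**4. Effect of surveying absentees.** In the fifth scenario, if 80% of skippers are surveyed anyway, the unsurveyed shares fall to 6% and 3%. The formula becomes 0.5 × 0.837 × (0.348 × 0.2/0.94 − 0.233 × 0.2/0.97) ≈ 0.011 SD. The simulation gave 0.012 to 0.014 SD and a type I error of 5.5%.

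**The case against.** The strongest reply is that this reads a rule into a condensed article. Nothing says that absentees are not surveyed, and make-up surveys may be described in a fuller protocol. The tablet sentence covers every time point, including T4 and T5, which have no session content, so it cannot be literally session-bound. This limits certainty about practice. It does not change what is written: T2 and T3 are defined by sessions and placed before their content in both arms, and the only remote route is attached to later visits.

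A reader might infer that people who skip a session leave the intent-to-treat comparison, turning it into one of attenders. The documents do not support that. Recruitment and Enrollment defines the enrolled set by consent and T1, and a mixed model keeps everyone with any score; a missed T2 costs that visit only.

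A reader might also take arm-dependent skipping as established. It is not. No attendance data are given, and the second meeting lasts about 90 minutes in both arms. Random skipping, even at unequal rates, and equally distress-related skipping at equal rates produced no clear bias. Bias needs skipping that is both outcome-related and different between arms.

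Finally, the plan does foresee missing data. It states its assumption, considers imputation, promises sensitivity analyses and lists attrition under Potential Limitations. However, the only sensitivity analysis described contrasts T1 to T3 with T4 to T5, which does not address outcome-dependent absence, and multiple imputation would ordinarily rest on the same assumption as REML.

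**Conclusion.** The point holds as a weakness in how the decisive outcomes are collected, not as a demonstrated bias. As written, scores at the only two post-baseline visits with an unexposed comparator depend on attending unblinded, arm-specific sessions, and the primary analysis would not correct absence that is outcome-related and unequal between arms.

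For distress-related skipping of 30% against 15%, the illustrative size is 0.05 to 0.09 SD, that is 0.05/0.3 = 17% to 0.09/0.3 = 30% of the planned effect. Confining distress-related skipping to the COPE arm is a more extreme case, at about 0.12 to 0.15 SD. All sizes rest on assumed skip rates, assumed correlations and the variance reading in the working. The direction could be reversed.

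**What to change.** In Overview and Study Design and in Intervention Arm: COPE, state that T2 and T3 are sought from every enrolled participant whether or not they attend, by emailing the existing Qualtrics survey to absentees. Use the same short calendar window around the scheduled session in both arms. The control-arm T3 must be completed before that participant receives any COPE content and, where possible, before the cluster's first COPE session; otherwise the last unexposed measurement is blurred. Record attendance, survey date and survey mode.

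Recruitment was due to end in spring 2025, so many clusters may already be past these visits. For them, report T2 and T3 completion by arm and attendance, and add a sensitivity analysis that shifts non-attenders' missing scores separately by arm. Results are expected by spring 2026.

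The cost is protocol wording, reminder emails and the gift card already budgeted per questionnaire. The downside is some mixing of survey mode and slight variation in timing at T2 and T3, which the recorded date and mode allow the analysis to examine.
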